### Ethical approval

The Central Adelaide Local Health Network Human Research Committee (CALHN-HREC) has approved the study (Approval No. 2023HRE00206). All participants will give informed consent before enrolment and randomisation. The treating surgeons or registrars will explain the information about the trial.

### Clinical trial registration

The study has been registered in the Australia New Zealand Clinical Trials Registry, and the trial number is ACTRN12623001273673.

### Statistical analysis

There are no studies investigating the improvement in gut microflora in patients with joint infections. Hence, we have based our sample size calculation on the superiority test. We assume a 10% difference in beta diversity between the groups will be a clinically meaningful change. Hence, for a mean difference of 0.1 with an assumed standard deviation of 0.075 at a 5% significance level and accounting for a 10% dropout rate, 80 patients will be required to demonstrate significant changes between the groups at 8 weeks. Normality will be assessed using the Shapiro-Wilk test. Mean and standard deviation or median and interquartile range will be reported. Paired t-test or Wilcoxon test will assess within-group differences, and an Independent t-test, or Mann-Whitney will assess the between-group differences. The secondary outcome measures investigating the outcomes from stool, blood and tissue specimens will be compared between the placebo and test cohorts using a paired t-test or Wilcoxon test for within-group differences and an Independent t-test or Mann-Whitney to investigate between-group differences. Results will be analysed on IBM SPSS 27.

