### Treatment allocation, randomisation and blinding

Patients who consent to participate will be enrolled in the study and assigned a code. Once enrolled, all patients will undergo standard-of-care treatment for their PJI, including optimisation by a multidisciplinary team comprising an anaesthetist, infectious diseases consultant, orthopaedic doctors, joint replacement nurses, dietitian, and post-surgical antibiotic therapy. Using a computer-generated block randomisation plan, one study investigator will randomly assign the patients to the placebo or intervention group. The treating surgeon and the patient will be blinded to the treatment allocation. Supplementation will start soon after the first-stage revision surgery when the patient is well enough to take oral foods. Based on the randomisation plan, the recruited patients will receive one sachet of test or control product mixed with milk, juice or food of their choice once a day for eight weeks. All in-patients will get the product with breakfast, supervised by the study dietitian. On discharge, patients will be given the clinical supplies to complete the supplementation daily for eight weeks. One of the investigators will ensure compliance through regular phone calls.

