### Outcomes measures

Primary outcome: The primary outcome is the change in gut microflora between the placebo and the test group after 8 weeks of supplementation.

Secondary outcomes: The study has several secondary outcomes, which are listed below:

Change in faecal calprotectin and short-chain fatty acids within and between cohorts at the end of 8-week supplementation.Change in Interleukin levels (IL-1, IL-6 and IL-10) within and between cohorts at the end of 8-week supplementation.Changes in C-reactive protein, CD4 and zonulin levels within and between the placebo and the test group at the end of 8-week supplementation.Tissue microbiology results will be compared between cohorts during first and second-stage surgery.Treatment outcomes using the Delphi criterion [33] (supplementary file 1) will be reported for the two cohorts at one and two years after second-stage surgery.

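### The primary endpoint has no defined per-patient variable: the trial is sized on beta diversity as a mean and SD and given univariate tests, but no distance measure, reference or patient-level summary is named

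*Protocol article*

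**What the plan says.** Under Outcomes measures the protocol article states: "The primary outcome is the change in gut microflora between the placebo and the test group after 8 weeks of supplementation". No index, distance or taxon is named there.

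Beta diversity appears only under Statistical analysis: "We assume a 10% difference in beta diversity between the groups will be a clinically meaningful change". It is treated as a quantity with a group mean and SD, "for a mean difference of 0.1 with an assumed standard deviation of 0.075", "at a 5% significance level" and "accounting for a 10% dropout rate", leading to "80 patients will be required to demonstrate significant changes between the groups at 8 weeks".

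The tests follow in the same paragraph: paired t or Wilcoxon within groups, and "an Independent t-test, or Mann-Whitney will assess the between-group differences". A later sentence repeats these tests for the secondary outcomes, so by implication the first statement covers the primary outcome.

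Under Stool samples, specimens are taken at t0, t4, t8 and second-stage surgery. The microbiome analysis described there is an R package and taxon abundances at phylum, genus and species level. No distance-based analysis is described anywhere in the article.

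**The concern.** Beta diversity describes how unlike two samples are. A mean, an SD and a two-sample t-test each need one independent value per patient. To get from one to the other, someone must choose a distance measure and say what each patient's sample is compared with: the patient's own baseline, a fixed reference, or the other patients. The article makes none of these choices.

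Two things are at stake. First, a primary result whose metric is open can be chosen after the data are seen, which weakens any claim made from its p-value. Second, the possible choices do not have the same error rate. Some are valid with the named tests; at least one, pooling pairwise distances within arms, is badly invalid.

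There is also a question of meaning. A distance has no direction. It can show that the community moved, not that it moved for the better, while the Hypothesis section speaks of better gut health.

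**Working it through.** **1. The plan's own figure.** Inputs from Statistical analysis: difference 0.1, SD 0.075, 5% significance, 10% dropout. Power, sidedness and allocation ratio are not stated; I assume two-sided and 1:1. With one value per patient,

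n per arm = 2 × (z₀.₉₇₅ + z_power)² × (SD/difference)²

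- 80% power: 2 × (1.960 + 0.842)² × (0.75)² = 8.8, so 9 per arm, 18 in total, 18/0.9 = 20 with dropout.
- 90% power: 2 × (1.960 + 1.282)² × (0.75)² = 11.8, so 12 per arm, 24 in total, 24/0.9 = 27 with dropout.

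The stated 80 is not reproduced. It would be reached at 80% power if the difference were 0.05: 2 × 7.85 × (1.5)² = 35.3, so 36 per arm, 72 in total, 72/0.9 = 80. The article does not say this. The discrepancy is a separate matter. It is shown here because it means that the sizing sentence cannot be used to work out which variable was intended.

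**2. Can the named tests be attached to a variable?**

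| Possible meaning of beta diversity | Independent t / Mann-Whitney | Paired t / Wilcoxon | Given in the article? |
|---|---|---|---|
| Each patient's own t0-to-t8 distance | valid, one value per patient | not applicable, nothing to pair | samples collected; distance not named |
| Distance of each sample to a fixed reference, at t0 and t8 | valid | valid | no reference named |
| All pairwise distances within each arm at t8 | invalid, values share patients | not applicable | not stated |

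Only the second reading fits both named tests, and it needs a reference that the article does not give.

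**3. How much the choice matters.** Evaluable patients: 80 × 0.9 = 72, or 36 per arm. Pairwise distances within one arm: 36 × 35 / 2 = 630, with each patient entering 35 of them. A t-test on these treats 36 independent patients as 630 independent observations.

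Null simulations with no arm effect, Bray-Curtis distance and 36 per arm, under two set-ups:

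| Analysis | Set-up A: Dirichlet compositions, 60 taxa, 600 to 1,000 runs | Set-up B: Dirichlet compositions, 50 taxa, 1,000 runs |
|---|---|---|
| One t0-to-t8 distance per patient, t-test | 4.3% to 6.8% | 4.6% |
| Within-arm pairwise distances, t-test | 57.7% to 69.3% | 63.6% |
| Within-arm pairwise distances, Mann-Whitney | 58% to 69% | not run |

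The number of taxa and the abundance model are assumptions; the article gives neither. Not every pairwise contrast is inflated: in set-up B, comparing cross-arm distances with the pooled within-arm distances of both arms rejected in 2.4% of runs. In set-up A, comparing placebo-placebo with cross-arm distances rejected in 38% to 49%. The error rate thus depends on a choice that the article leaves open.

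**The case against.** The strongest reply is that the article counts patients, not pairs: a mean difference, an SD, a dropout rate and a total of 80. That suggests one value per patient. The outcome is worded as a change, and t0 and t8 stool are both collected, so a per-patient t0-to-t8 distance can be computed and the named independent test is valid for it. This stands. A reader might infer that beta diversity has no per-patient value and that the stated test is therefore invalid. The documents do not support that.

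A reader might also infer that this trial faces a false-positive rate near 60%. That is not supported either. No section says that pairwise distances will be pooled, and the figure rests on that reading and on an assumed taxa model.

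Nor is the choice of primary metric wholly free: the sizing paragraph ties it to beta diversity at 8 weeks. What stays open is the distance, the reference and the summary, and the outcome statement does not repeat even the words beta diversity.

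Finally, this is a journal article, and the choice of distance or R routine is often left to a fuller document. That excuses missing detail. It does not remove the printed mismatch: the article commits to a variable and to a set of tests, and the most natural per-patient version of that variable cannot take the paired test. A fuller document would have to supply the definition and amend the test list.

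**Conclusion.** The point holds as a defect in the definition of the primary endpoint. The outcome names no metric, the sizing uses a between-sample dissimilarity as if it were a patient-level score, and the named tests match no defined variable. The primary analysis cannot be run without a choice that the article does not make.

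The conclusion rests on the article's text and on what beta diversity is, not on the simulations. Their role is limited: they show that one possible choice keeps the nominal 5% while another raises it to about 60%, under an assumed taxa model and 36 patients per arm at 1:1. The inflation is conditional on pooling within-arm pairwise distances.

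The sizing is not endorsed. Even with a valid per-patient scalar, the stated inputs give 20 patients at 80% power or 27 at 90%, two-sided and after dropout, and nothing in the article ties an SD of 0.075 to any particular distance.

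**What to change.** Before unblinding, amend Outcomes measures and Statistical analysis to:

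- **Name one primary scalar per patient.** For example, the Bray-Curtis distance between that patient's t0 and t8 samples, compared between arms with the independent test already named. A distance to a stated fixed reference would also be valid.
- **Drop the paired within-group test for this scalar.** With a t0-to-t8 distance there is only one value per patient.
- **Add PERMANOVA on t8 composition, permuting patients,** as the supporting analysis.
- **State that no t-test or Mann-Whitney is run on pairwise distances.**
- **Limit the primary conclusion to a change in composition.** Support any claim of improvement with a named directional measure already listed as a secondary outcome, such as faecal short-chain fatty acids, which stays secondary.

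The cost is wording in the protocol and analysis plan and standard R routines; R is already planned for the microbiome work. No new samples are needed. The mismatch between the stated inputs and 80 patients must be resolved separately, and this change does not validate the sample size.

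### The printed sample-size inputs (difference 0.1, SD 0.075, 5% level, 10% dropout) do not give 80 patients at any conventional power, and no power is stated

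*Protocol article*

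**What the plan says.** The sample-size reasoning is in the Statistical analysis section of the protocol article. It opens by saying that "we have based our sample size calculation on the superiority test". It then sets the target: "We assume a 10% difference in beta diversity between the groups will be a clinically meaningful change". The numerical inputs follow as "a mean difference of 0.1 with an assumed standard deviation of 0.075 at a 5% significance level", and the calculation is described as "accounting for a 10% dropout rate". The conclusion is that "80 patients will be required to demonstrate significant changes between the groups at 8 weeks".

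The same section names the comparison to be made between arms: "an Independent t-test, or Mann-Whitney will assess the between-group differences". The Abstract and the section on study design and products both repeat 80 as the number randomised. The article gives no power, sidedness, allocation ratio or superiority margin.

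**The concern.** A difference of 0.1 against an SD of 0.075 is a very large standardised effect, 1.33 SDs. An effect of that size needs only a few tens of patients, so a requirement of 80 looks too high by a factor of about three at usual power. Because the power is missing, a reader cannot tell whether an unusual power level or some other input explains the gap.

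What is at stake is the meaning of the design. If the printed inputs hold, the trial is almost certain to detect its target and can absorb substantial losses. If the SD in the underlying calculation was larger, or the difference smaller, the same 80 patients may give only ordinary power. The reserve matters here because the Data collection section removes participants with under 80% compliance from the final analyses, while the calculation allows for a 10% loss only.

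**Working it through.** **Inputs from the Statistical analysis section:** difference Δ = 0.1; SD σ = 0.075; α = 0.05; dropout 10%.

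**Assumptions, not in the article:** two-sided test, 1:1 allocation, no margin, and a range of powers.

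**Step 1. Standardised effect.** d = Δ/σ = 0.1/0.075 = 1.333.

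**Step 2. Attempt to reproduce 80 from the printed inputs.** By normal approximation, n per arm = 2(z₀.₉₇₅ + z_power)²/d². At 80% power this is 2 × (1.960 + 0.842)²/1.778 = 8.8, so 9 per arm, 18 evaluable, and 18/0.9 = 20 in total. The exact two-sample t calculation gives 9.9, so 10 per arm, and 20/0.9 = 22.2, so 23 in total. Other powers follow in the same way:

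| Power | n per arm, normal | Total after 10% dropout | n per arm, exact t | Total after 10% dropout |
|---|---|---|---|---|
| 80% | 9 | 20 | 10 | 23 |
| 90% | 12 | 27 | 13 | 29 |
| 95% | 15 | 34 | 16 | 36 |
| 99% | 21 | 47 | 22 | 49 |
| 99.9% | 29 | 65 | 30 | 67 |

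Keeping the arms equal in size adds at most one patient to each total.

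**Step 3. Other conventions.** A one-sided 5% test lowers the need further (16 in total at 80% power and 23 at 90%, normal approximation). Multiplying by 1.1 for dropout instead of dividing by 0.9 hardly changes the totals. The section also allows a Mann-Whitney test. Inflating by its worst-case efficiency (1/0.864) reaches 78 only when combined with two-sided testing, 99.9% power and the exact t calculation. No conventional choice returns 80.

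**Step 4. What would return 80.** With 80 randomised and 10% lost, 72 are evaluable, 36 per arm. At two-sided 5% and 80% power, a standardised effect of 0.667 gives 2 × (1.960 + 0.842)²/0.444 = 35.3, so 36 per arm and 72/0.9 = 80 exactly. (The exact t calculation gives 36.3, so 37 per arm, and 74/0.9 = 82.2, so 83.) Three input sets produce that effect:

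- Δ = 0.1 with SD 0.15: 0.1/0.15 = 0.667;
- Δ = 0.05 with SD 0.075: 0.05/0.075 = 0.667;
- the printed Δ = 0.1 and SD 0.075 with an unstated superiority margin of 0.05 (one-sided 2.5%): (0.1 − 0.05)/0.075 = 0.667.

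These depend on the assumed 80% power. At 90% power, 36 per arm corresponds to an SD of about 0.131 with Δ = 0.1, or to Δ of about 0.057 with SD 0.075. At 95% the figures are about 0.118 and 0.064.

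**Step 5. What 36 evaluable per arm delivers for Δ = 0.1** (two-sided 5% t-test; the SDs other than 0.075 are assumed values):

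| SD | Power |
|---|---|
| 0.075 (printed) | 99.99% |
| 0.10 | 98.7% |
| 0.15 | 79.7% |
| 0.20 | 55.3% |

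**The case against.** The strongest reply is that the mismatch does no harm. With the printed inputs, 80 is more than enough, and the Discussion presents the trial as a single-centre proof of concept with an estimated sample size. Sidedness and allocation ratio may also stand in the full protocol, which an article condenses. Both points are fair. They limit the consequence and the list of omissions to complain about. They do not remove the fault, because the article itself prints the inputs and the result, and these disagree.

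Several stronger readings are tempting but not supported:

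- **That one printed input is off by a factor of two.** This holds only at an assumed 80% power with no margin. At 90% power the matching SD is about 0.131, which is 1.75 times the printed one. The section refers to a superiority test, and an unreported margin of 0.05 would return 80 with both printed inputs correct. An omission is as possible as a misprint.
- **That the 10% is really a relative change and so a smaller absolute one.** The article itself equates 10% with 0.1 and gives no mean beta diversity from which a relative change could be worked out.
- **That a null result would mean something entirely different under each reading.** Once data exist, a null result is read from the observed estimate and its confidence interval, not from the planning SD.
- **That the trial is underpowered, or enrols a definite number of surplus patients.** The first depends on an SD the article does not state. The second depends on a power it does not state.

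**Conclusion.** The concern stands in a limited form. The statement that 80 patients are required is wrong for the inputs beside it, which need roughly 20–23 at 80% power, 27–29 at 90% and 47–49 at 99%. This rests on two-sided testing and 1:1 allocation; one-sided testing would widen the gap. The missing power prevents a reader from resolving it.

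The cause cannot be established from the article. Either an input is misreported or omitted, or 80 was set on other grounds. The input sets in the working that return 80 are inferences.

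The practical effect also depends on the cause. With the printed inputs the trial has ample power. With an SD of 0.15 it has about 80% and nothing in hand for losses beyond the 10% allowed. The arithmetic is certain and the correction is cheap, so the paragraph should be put right.

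**What to change.** Keep 80 and restate the sample-size paragraph. Report the power, the sidedness, any superiority margin, and the difference and SD that were actually used, so that the calculation returns 80. If 80 was set on other grounds, such as expected recruitment, say so and give the power it delivers. The inputs should come from the original calculation and not be chosen afterwards to fit 80.

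Add one line on sensitivity to the SD, labelled as an assumed range. For a difference of 0.1 with 36 evaluable per arm, power runs from 99.99% at SD 0.075 through about 80% at 0.15 to 55% at 0.20.

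The cost is the rewording of one paragraph, with no extra patients. The downside is that the stated operating characteristics may look less favourable than the printed inputs imply.

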#### Dietary pattern

Patients’ dietary patterns at baseline will be collected using a food frequency questionnaire screener (FFS) validated for the Australian population and a 4-day Food Diary by the study dietitian (AM). The patients who habitually consume a higher-fibre diet may have a significantly different microbiome profile than those who consume a lower-fibre diet. Hence, this tool will allow us to identify the added effect of prebiotic fibre.

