To our knowledge, only one clinical study has investigated gut dysbiosis directly in PJI patients. This recent study reported significantly (*p* < 0.001) higher levels of Zonulin, a marker of increased gut-permeability, in PJI patients (7.6 ± 6.1 ng/ml) as compared to primary arthroplasty patients (3.9 ± 4.5 ng/ml) [40]. While this study used surrogate markers of gut permeability, pilot data generated at our hospital (unpublished) suggests the existence of gut dysbiosis in PJI patients. In the current study, we will administer resistant starch or placebo to PJI patients for eight weeks and investigate the changes in the gut microbiome. In addition, an array of plasma inflammatory and gut permeability markers and blood microbiomes will be measured. Apart from directly assessing gut dysbiosis, this study will also evaluate if the dysbiosis can be reset through prebiotic intervention.

There are some limitations in the design of this study. Firstly, this is a single-centre study with an estimated sample size. It is clinically and ethically essential to generate proof of concept data before any large-scale interventions can be planned. If the results from this initial study are promising, we will undertake a multicentre study to validate the findings. Secondly, the impact of change in gut microbiome on surgical outcomes will be evaluated one and two years after the second stage revision. Due to the nature of PJI, many patients may not be able to make it to the longer-term follow-up either due to premature death or non-resolution of infection, thus requiring several repeat first-stage surgeries, or may not be medically fit to undergo second-stage revision due to comorbidities. Lastly, the patients will take the product at home (after discharge) and administer the intervention products. To encourage compliance, one of the study investigators will phone the patients regularly and empty packages will be returned to investigators.

In conclusion, this study’s findings will provide the first clinical evidence of targeting gut health to prevent and manage joint infections.

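### The stated between-arm tests use neither baseline value nor fibre intake as a covariate, and within-arm p-values count as part of comparing the arms

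*Protocol article*

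**What the plan says.** The Statistical analysis section of the protocol article names its tests. On distribution: "Normality will be assessed using the Shapiro-Wilk test". Within arms: "Paired t-test or Wilcoxon test will assess within-group differences". Between arms: "an Independent t-test, or Mann-Whitney will assess the between-group differences". No covariate appears, and the section does not say whether the two-sample test is applied to the change from t0 or to the t8 value.

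For the stool, blood and tissue secondary outcomes, the same section says they "will be compared between the placebo and test cohorts using a paired t-test or Wilcoxon test for within-group differences", and then adds the two-sample tests.

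Under Outcomes measures, the primary outcome is between arms only: "The primary outcome is the change in gut microflora between the placebo and the test group after 8 weeks of supplementation". The biomarker outcomes also include within-arm change, for example: "Change in faecal calprotectin and short-chain fatty acids within and between cohorts at the end of 8-week supplementation".

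Under Dietary pattern, baseline diet is recorded by a screener and a food diary. The reason given is that habitual fibre intake may go with a different microbiome, and that "this tool will allow us to identify the added effect of prebiotic fibre". No stated analysis takes diet as an input.

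**The concern.** Three features combine.

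- **Precision.** An outcome measured before and after treatment is usually estimated most precisely by modelling the week-8 value with the baseline value as covariate. The named tests cannot do this. The biomarkers have no sample size calculation, so lost precision may matter there.
- **Diet.** The article treats habitual fibre as an influence on the microbiome and gives the diet data a purpose, but no test it names can serve that purpose.
- **Within-arm tests.** All patients have first-stage surgery and antibiotics (Treatment allocation, randomisation and blinding), so inflammatory markers and flora can move in both arms whatever is in the sachet. A paired test within one arm detects that movement and compares nothing between arms. If it is listed as part of the comparison, a significant change in the supplement arm beside a non-significant one in the placebo arm is easily taken for a product effect.

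**Working it through.** **1. The plan's own figure.** Inputs from Statistical analysis: difference 0.1, SD 0.075, 5% level, 10% dropout, 80 patients. Power, sidedness and allocation ratio are not stated; I take two-sided and 1:1. By n per arm = 2(z₀.₉₇₅ + z_power)²(SD/difference)²:

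- 80% power: 2 × (1.960 + 0.842)² × 0.5625 = 8.8, so 9 per arm, 18 in all, 20 with dropout.
- 90% power: 24 in all, 27 with dropout. 99% power: 42 in all, 47 with dropout.

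None of these gives 80, which is a separate matter. What counts here is the power at 80 × 0.9 = 72 evaluable, or 36 per arm: Φ[(0.1/0.075) × √(36/2) − 1.96] = Φ(3.70) = 99.99%. On its stated inputs the primary test has power to spare without adjustment.

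**2. Precision.** Let r be the baseline to week-8 correlation, which the article does not give; I assume 0.3, 0.5 and 0.7, with equal variance at both times. Relative to the week-8 value alone (1), the variance is 2(1 − r) for a change score and 1 − r² for ANCOVA. ANCOVA over change score is therefore (1 + r)/2. The last column is power with 36 per arm for an assumed effect of 0.5 SD.

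| r | ANCOVA / week-8 only | ANCOVA / change score | Power: week-8 only / change / ANCOVA |
|---|---|---|---|
| 0.3 | 0.91 | 0.65 | 56% / 43% / 60% |
| 0.5 | 0.75 | 0.75 | 56% / 56% / 69% |
| 0.7 | 0.51 | 0.85 | 56% / 78% / 84% |

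Between the two unadjusted versions the article leaves open, power ranges from 43% against 56% (r = 0.3) to 78% against 56% (r = 0.7). ANCOVA is at least as precise as either in every row. Any further gain from fibre intake is not included, since the article gives no figure for it.

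**3. Within-arm tests.** Suppose no product effect and the same trend in both arms, so that each arm's paired test is significant with probability p, independently. The chance that only the supplement arm is significant is p(1 − p):

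- p = 0.3: 0.3 × 0.7 = 21%
- p = 0.5: 0.5 × 0.5 = 25%
- p = 0.8: 0.8 × 0.2 = 16%

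A simulation agrees (20,000 trials per setting, 36 per arm, no product effect, r from 0.3 to 0.7). With an assumed common trend of 0.25 to 0.5 SD, the supplement arm's paired test was significant in 24% to 97% of trials, and significant in that arm alone in about 4% to 25%. The between-arm t-test stayed at about 5% throughout.

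**The case against.** Much can be said for the plan.

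- **Baseline is not thrown away.** A reader might infer that the t0 values go unused. The documents do not support that: Outcomes measures defines the primary and biomarker outcomes as change, a two-sample test on change uses t0, and so do the paired tests. What remains is that t0 is not a covariate and that the analysed quantity is not stated.
- **The primary comparison is not biased.** A reader might also infer that recovery over time could pass for a product effect there. A trend shared by randomised arms cancels in the between-arm test, and chance imbalance in fibre intake is already allowed for in its standard error. The hazard lies only in the within-arm tests, which always accompany a between-arm test. No text says conclusions will rest on them.
- **The discordance is smaller than it may look.** Counting trials in which either arm alone is significant gives 2p(1 − p), or 42%, 50% and 32%. Half of those favour placebo and would not be read as benefit.
- **Selection of the test by Shapiro-Wilk is implied, not stated.** It is a fair reading, because the normality check sits beside paired alternatives and has no other stated use beyond the choice of summary statistics.
- **Evidence of skew is limited.** The zonulin levels quoted in the Discussion, "in PJI patients (7.6 ± 6.1 ng/ml) as compared to primary arthroplasty patients (3.9 ± 4.5 ng/ml", have SD/mean of 6.1/7.6 = 0.80 and 4.5/3.9 = 1.15. They are raw levels of one marker from another study, and the SD above the mean belongs to the non-infected group. They make skew foreseeable for zonulin and prove nothing about changes or other markers.
- **An analysis plan may hold more.** Covariate lists and the use of week-4 samples are often left to it, and I raise neither as an omission. But this article names the tests, gives within-arm tests a comparative role and gives diet a purpose that no test serves. Those points stand.

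**Conclusion.** The concern holds in limited form: the plan should be changed, but the primary test is not invalid. The between-arm test keeps its error rate of about 5%, provided the analysed groups are comparable as randomised. The compliance exclusion under Data collection bears on that proviso and is a separate question.

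The cost is precision. ANCOVA variance is 15% to 35% below a change-score test and 9% to 49% below a week-8-only test, for assumed correlations of 0.3 to 0.7. On the stated inputs this does not endanger the primary test. It counts for the biomarkers, or if the true effect is smaller or the SD larger than assumed.

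The within-arm p-values are the part that can mislead: a supplement-only significant result arises in 16% to 25% of trials with no product effect, for within-arm power of 30% to 80%. The correlations, trends, within-arm power and 0.5 SD effect are my assumptions and not document figures.

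**What to change.** 1. For each continuous per-patient stool marker, make the single between-arm analysis an ANCOVA of the t8 value on arm, t0 value and baseline fibre intake. Report the adjusted difference with its 95% CI.
2. Do the same for each blood marker that has both a baseline and a week-8 sample. The article must first be reconciled on this: the Abstract has blood taken at baseline, four weeks, eight weeks and second-stage surgery, while Blood and bone tissue collection describes intra-operative draws only. The schedule table and design figure, which may settle it, are not legible in the text at hand.
3. Fix the scale of each marker in advance, with logs for those expected to be skewed and the effect then given as a ratio of geometric means. Keep a rank test as sensitivity analysis, not chosen by a normality test on the same data.
4. Take within-arm change out of the outcome definitions and out of the sentence on comparing cohorts. Show it descriptively without p-values, and base conclusions on the between-arm estimate.
5. Do not apply item 1 mechanically to beta diversity. It measures dissimilarity between samples and has no obvious single baseline value per patient, so the quantity analysed must be defined first.

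For the stool markers this is a change of wording: t0, t8 and diet are already collected. For blood it costs no more if the Abstract's schedule is the operative one; otherwise the model cannot be fitted to those markers.
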